## Abstract

Adequate sleep health is critical for surgical recovery. Disrupted sleep can impede wound healing and cognitive performance and contribute to poor surgical outcomes. Preoperative intervention aimed at improving surgical outcomes is often referred to as prehabilitation and commonly uses exercise, nutrition or psychological intervention. Sleep prehabilitation interventions have not yet been studied. This randomised assessor‐blinded trial will measure the effect of a personalised sleep prehabilitation (PSP) intervention in addition to standard of care prehabilitation (PREHAB) on participant sleep health compared to PREHAB alone (Clinicaltrials.gov ID: NCT06762639). One hundred fifty‐four English‐speaking patients from the University Health Network's Prehabilitation Program with sleep disturbance and a surgery within 4–12 weeks will be recruited. Patients will be excluded if they are participating in PREHAB remotely, have an existing sleep disorder, are a shift worker, have travel plans outside of their usual time zone or have a cognitive disability that precludes participation. Study assessments occur at baseline, 1 week before surgery and 6 weeks after surgery. PREHAB consists of individualised exercise and nutrition support as well as psychological intervention. The PSP consists of a baseline sleep assessment, brief behavioural treatment for insomnia (BBTI), sleep hygiene and behaviour‐change support. The primary outcome is the Pittsburgh Sleep Quality Index (PSQI). The primary analysis will be an ANCOVA to detect differences in PSQI between groups 1 week before surgery whilst controlling for baseline scores. The proposed study will be the first to explore the effect of a personalised preoperative sleep intervention.

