### Sample Size

3.3

A total of 154 participants will be recruited for this study. The sample size was computed by a biostatistician at UHN for an ANCOVA design in which the Pittsburgh Sleep Quality Index (PSQI) score will be compared between the two arms at the preoperative timepoint, controlling for baseline scores. Assuming a PSQI score mean of 11.9 (SD 2.6) points for the usual care arm (Atoui et al. 2023) with no correlation between baseline and preoperative scores, a sample size of 64 participants per arm (128 total) will be required to detect a difference in mean PSQI score of 1.3 points, which is the minimum clinically important difference (Longo et al. 2021). This difference between the two arms corresponds to a Cohen's d effect size of 0.5 with 80% power and an alpha of 0.05. The final sample accounts for 20% attrition.

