### Analytic Plan

4.1

All data will be collected and imported into R version 4.1.2 for statistical analysis; an alpha of 0.05 will be used. Participant characteristics will be summarised using means (SD) or medians [IQR] for continuous variables and frequency (%) for categorical variables. We will report reasons for exclusion and attrition, as well as safety or adverse events with frequency and percentages.

The statistical analysis plan was created in consultation with a UHN biostatistician. The primary outcome (PSQI score) will be compared between the two treatment arms using analysis of covariance (ANCOVA), controlling for baseline PSQI score. A linear mixed effects model will be used to compare treatment arms with respect to the longitudinal PSQI scores (baseline, preoperative, 6 weeks post‐surgery). Point estimates and 95% confidence intervals will be calculated for changes in the PSQI between groups at each timepoint. We will use Q–Q plots and histograms to assess data normality. If non‐normality is encountered and cannot be corrected through data transformations (e.g., log, square root), we will employ appropriate non‐parametric alternatives, such as the Mann–Whitney U test for between‐group comparison. Model assumptions including homogeneity of variance (Levene's Test) and normality of dependent variables (Shapiro–Wilk Test) will be used. Independence of observations was assessed using the Durbin Watson (DW) statistic, with values between 1.5 and 2.5 indicating independence. Sensitivity analyses will address potential loss to follow‐up by replacing the missing outcome measurements with best or worst values to assess the robustness of our results. In the unlikely event of unbalanced baseline characteristics between the treatment arms, the mixed effects models will be adjusted for these potential confounders (e.g., age, sex, etc.). Conclusions will be drawn using comparisons of each time point between groups. The minimum clinically important difference for the PSQI score will be 1.3 based on previous research (Shergis et al. 2016). Given a lack of consensus for the PSQI MCID, previous research has interpreted any statistically significant change in the PSQI to be clinically meaningful (Shergis et al. 2016).

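### The plan names and sizes one primary test at the preoperative visit, but Section 4.1 draws conclusions from PSQI comparisons at each time point, with no hierarchy or error control among them

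*Protocol article*

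**What the plan says.** Three places in the protocol article bear on which result decides the trial.

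- **Abstract:** "The primary analysis will be an ANCOVA to detect differences in PSQI between groups 1 week before surgery whilst controlling for baseline scores". This is one outcome, one visit and one model.
- **Section 3.3, Sample Size:** the PSQI "score will be compared between the two arms at the preoperative timepoint, controlling for baseline scores". The calculation has an "effect size of 0.5 with 80% power and an alpha of 0.05" and gives 64 evaluable participants per arm.
- **Section 4.1, Analytic Plan:** "an alpha of 0.05 will be used" throughout. The section restates the baseline-adjusted ANCOVA, this time without its visit, and adds a linear mixed model over baseline, preoperative and 6-week PSQI scores. It continues: "Point estimates and 95% confidence intervals will be calculated for changes in the PSQI between groups at each timepoint". Later in the same paragraph comes the rule at issue: "Conclusions will be drawn using comparisons of each time point between groups".

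The only multiplicity adjustment is in the last paragraph of Section 4.1. It applies a Bonferroni correction to secondary outcomes, which are described as exploratory. The PSQI is the primary outcome, and the article nowhere classes the 6-week PSQI as secondary.

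**The concern.** The Abstract and Section 3.3 fix a single confirmatory comparison. The sentence in Section 4.1 is worded as a rule for reaching conclusions, and it points to every visit without singling one out. The two do not agree.

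Two things are at stake.

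- **The error rate of the headline claim.** A 5% rate belongs to the single preoperative test. It does not carry over to a claim that could rest on whichever post-randomisation visit is significant. Section 4.1 also cites earlier work that took any significant PSQI change as clinically meaningful, so a significant result at either visit could readily be read as success.
- **A defined answer.** The plan does not say what is concluded if the ANCOVA and the mixed model differ at the preoperative visit, or if only one of the two visits shows a difference.

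This is not detail left to an unseen analysis plan. An analysis plan could not follow both the Abstract and this sentence as they are written.

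**Working it through.** **Step 1. Reproduce the plan's own figure.** The inputs are from Section 3.3: SD 2.6, difference 1.3, power 80%, alpha 0.05. Sidedness is not stated; two-sided reproduces the result. With zero correlation between baseline and preoperative scores, as the section assumes, ANCOVA gains nothing from the covariate and the calculation is that of a two-sample comparison.

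- Effect size: 1.3 / 2.6 = 0.5.
- Normal approximation: n per arm = 2 × (1.960 + 0.842)² / 0.5² = 62.8, so 63.
- t distribution: 63.8, so 64 per arm. Power at 64 per arm is 80.1%.

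The stated 64 per arm is therefore the size for **one** test at two-sided 0.05.

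**Step 2. Error if either post-randomisation visit could carry the claim.** Take two two-sided tests at 0.05, preoperative and 6 weeks, with no effect at either visit.

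- Independent tests: 1 − (1 − 0.05)² = 0.0975.
- Correlated tests: 1 − P(|Z₁| ≤ 1.96 and |Z₂| ≤ 1.96), with Z₁ and Z₂ bivariate normal with correlation r, from a simulation of 2 million draws.

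| r (assumed) | Family-wise error |
|---|---|
| 0 | 9.8% |
| 0.3 | 9.5% |
| 0.5 | 9.1% |
| 0.7 | 8.3% |
| 0.9 | 7.0% |

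The article gives no correlation between the visits, so r is varied. Two PSQI results from the same patients are unlikely to be independent, so the top row is an upper end rather than a best guess. The error exceeds 5% in every row. The further choice between ANCOVA and mixed model at the preoperative visit is not counted.

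**Step 3. What each remedy costs.**

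- *Preoperative ANCOVA as the only confirmatory test:* alpha stays at 0.05 and power at 64 per arm stays at 80.1%.
- *Alpha split equally over the two visits (0.025 each):* family-wise error is at most 5%, but power per test at 64 per arm falls to 71.2%. Restoring 80% needs 78 per arm (2 × 78 = 156 evaluable instead of 128).

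The first option matches what the Abstract and Section 3.3 already say.

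**The case against.** The best defence is that a hierarchy already exists. The Abstract names one primary analysis, Section 3.3 sizes the trial for it, and secondary outcomes are labelled exploratory and adjusted. Nowhere does the article say that the 6-week visit or the mixed model may by itself establish success. The disputed sentence directly follows one about adjusting the mixed models, so it may mean only that those models are read through between-group contrasts at each visit. That milder reading is plausible, and on it the defect is ambiguity rather than a second decision rule. But the sentence is not limited to the mixed model, and nothing in Section 4.1 reserves the effectiveness conclusion for the preoperative ANCOVA. The need to reconcile the passages stands.

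One could also argue that the 6-week PSQI falls under the Bonferroni rule. The text does not say so.

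Three stronger readings are tempting, and the article does not support them.

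- *The contrasts behind the conclusion were not powered.* A plain between-group comparison at the preoperative visit has about 80% power at 64 per arm, and under the plan's zero-correlation assumption it is as precise as the ANCOVA. Only the 6-week comparison was not sized.
- *The mixed model loses power by contrasting changes from baseline.* That would depend on how baseline enters the model, which the article does not state and may leave to the full analysis plan. The primary ANCOVA is unaffected either way.
- *A baseline significance test is planned.* Baseline is among the mixed model's time points, but no such test is explicitly stated, and a change at baseline has no meaning. It is enough for the replacement wording to rule one out, since a baseline difference under randomisation says nothing about efficacy.

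**Conclusion.** The conflict is real. The Abstract and Section 3.3 define one primary test at one visit. Section 4.1 bases conclusions on each time point and gives no order or alpha control for the PSQI comparisons. If either post-randomisation visit could support the claim, the family-wise error would be between about 7.0% (correlation 0.9) and 9.8% (independence) instead of 5%. That range rests on two assumptions: the correlations, which the article does not give, and an either-visit rule, which the sentence leaves open but does not state outright. It should not be read as the error rate of the preoperative ANCOVA, which remains 5%. The lack of a stated answer when models or visits disagree depends on neither assumption.

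**What to change.** Replace the sentence in Section 4.1 with wording such as:

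> The conclusion on effectiveness rests only on the baseline-adjusted ANCOVA difference in PSQI at the preoperative visit. The mixed-model and 6-week PSQI contrasts are secondary and supportive; the 6-week contrast is tested at 0.05 only if the preoperative result is significant. Baseline is described, not tested.

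As an alternative to testing in sequence, the 6-week contrast can be placed in the Bonferroni family for secondary outcomes. Either choice works if it is written down before data are seen. Naming the preoperative visit where Section 4.1 describes the ANCOVA would bring all three places into line.

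The cost is wording only. Alpha stays at 0.05, and 64 evaluable per arm keeps 80% power. The small downside is that an effect seen only at 6 weeks cannot support the primary claim.

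Giving both arms a common baseline mean in the PSQI mixed model is an optional gain in precision. It does not correct an error shown in the text.

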Additional exploratory analyses using linear mixed effect models will be conducted to understand the effect of the intervention on secondary outcomes that are measured longitudinally, including physical fitness (e.g., 6MWT) outcomes and the PROMIS‐29+2. For outcomes that are measured at only one time point (e.g., length of hospital stay), we will use non‐parametric Wilcoxon signed‐rank *t*‐tests or Chi‐square tests for continuous and categorical outcomes, respectively. Given the exploratory nature of secondary outcomes, *p*‐values will be adjusted using Bonferroni corrections to account for multiple comparisons. All analyses will be conducted using the intention to treat principle. The data will be reported in accordance with the Consolidated Standards of Reporting Trials (CONSORT) guidelines for reporting randomised trials (Schulz et al. 2010).

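### Section 4.1 draws PSQI conclusions from every time point at 0.05 with no order, which conflicts with the single preoperative ANCOVA on which the trial is sized

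*Protocol article*

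**What the plan says.** The Abstract names one decisive test: "The primary analysis will be an ANCOVA to detect differences in PSQI between groups 1 week before surgery whilst controlling for baseline scores". Section 3.3 (Sample Size) is built on the same preoperative comparison: "a sample size of 64 participants per arm (128 total) will be required to detect a difference in mean PSQI score", corresponding to an "effect size of 0.5 with 80% power and an alpha of 0.05".

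Section 4.1 (Analytic Plan) sets a general rule that "an alpha of 0.05 will be used". It gives the ANCOVA for the PSQI without naming its time point, then a linear mixed model over baseline, preoperative and 6-week scores, with 95% intervals for the arm difference at each visit. Shortly afterwards it states the basis for inference: "Conclusions will be drawn using comparisons of each time point between groups".

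The only multiplicity rule is at the end of section 4.1, where "values will be adjusted using Bonferroni corrections to account for multiple comparisons". That sentence is tied to secondary outcomes. Table 2 labels the PSQI as the primary outcome in a single row marked at baseline, T1 and 6 weeks.

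**The concern.** There are two statements about what supports the PSQI conclusion. One is a single test at a single visit; the other is a set of comparisons at all visits, each at 0.05, with no hierarchy. Nothing within section 4.1 ranks the preoperative visit above the 6-week visit.

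At stake is what may be claimed if the results differ by visit. A trial that misses on its powered T1 ANCOVA could, under the quoted sentence, still conclude that the intervention improves the PSQI because the 6-week interval excludes zero. Section 4.1 also mentions that earlier research took any significant PSQI change as clinically meaningful. The protocol does not say that it adopts this, but a lone 6-week result could be presented in that light.

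**Working it through.** **Inputs.** From section 3.3: difference 1.3 points, SD 2.6, no correlation between baseline and preoperative scores, 64 evaluable per arm, 80% power, alpha 0.05. From section 4.1: alpha 0.05 for all analyses; three PSQI time points, two of them after baseline. Assumed here: two-sided tests, a common correlation r between visits (0 to 0.7), and the form of the mixed-model contrast, which the article does not give.

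**1. The plan's own figure.** d = 1.3 / 2.6 = 0.5. The normal approximation gives n = 2(1.960 + 0.842)² / 0.5² = 62.8, so 63 per arm. With the noncentral t, 63 per arm has 79.5% power and 64 has 80.1%. The stated 64 per arm is reproduced for one two-sided test at 0.05. A one-sided test would need only 2(1.645 + 0.842)² / 0.25 = 49.5, so 50 per arm; two-sided is therefore the right reading.

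**2. Two post-baseline PSQI tests, each at 0.05, no effect at either visit.**
- Independent: 1 − 0.95² = 9.75%.
- Upper limit under any dependence: 0.05 + 0.05 = 10%.
- Correlation between the two test statistics of 0.5: 9.1%. Correlation of 0.7: 8.4%.

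With equal correlation r between visits and adjustment for baseline, the correlation between the T1 and 6-week tests is (r − r²)/(1 − r²) = r/(1 + r). This is 0.23, 0.33 and 0.41 for r = 0.3, 0.5 and 0.7. The tests therefore stay only modestly correlated, and the rate remains above 9%.

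**3. Null simulation of the trial.** 64 per arm, 40,000 replicates per row, Monte Carlo standard error about 0.15 percentage points. Entries are the chance that at least one of the listed tests has p < 0.05.

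| r | ANCOVA T1; ANCOVA 6 weeks | ANCOVA T1; unadjusted 6 weeks | ANCOVA T1; unadjusted T1 and 6 weeks | ANCOVA T1; change from baseline at T1 and 6 weeks |
|---|---|---|---|---|
| 0 | 9.76% | 9.83% | 10.14% | 12.10% |
| 0.3 | 9.53% | 9.55% | 10.70% | 11.59% |
| 0.5 | 9.60% | 9.66% | 11.42% | 11.50% |
| 0.7 | 9.45% | 9.50% | 11.58% | 10.97% |

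The first two result columns count each post-baseline visit once and give 9-10%. The last two count T1 twice, through the ANCOVA and through a mixed-model contrast that does not adjust for baseline in the same way, and give 10-12%.

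**4. With one deciding test.** If only the T1 ANCOVA supports the conclusion, or if the 6-week contrast is tested only after T1 is significant, the chance of any false PSQI claim is at most 5%.

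**The case against.** The strongest reply is that the primary analysis is already fixed. The Abstract names it, section 3.3 is sized on it, and section 4.1 lists the ANCOVA first. The sentence on conclusions comes directly after one about adjusting the mixed models, so it may only describe how the longitudinal model will be read: between arms at each visit, not within arms. A separate analysis plan or the appendix of research questions, neither of which is shown, may class the 6-week PSQI as secondary, which would bring it under the Bonferroni rule.

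Part of this stands. The milder reading is possible, and exclusion from the Bonferroni rule is an inference from the primary-outcome label in Table 2. But the sentence as printed is a rule about conclusions and puts all visits on an equal footing. It is a stated rule that conflicts with the Abstract and section 3.3, so it needs correcting whatever another document adds.

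Three stronger readings go further than the document supports:
- **That the primary test is inflated.** It is not. The T1 ANCOVA keeps its 5%; the excess belongs to the wider event of any PSQI claim.
- **That the false-claim rate is up to 15%.** That needs the baseline comparison to be counted (1 − 0.95³ = 14.3%, limit 15%). A baseline difference between randomised arms cannot be a claim that the intervention worked.
- **That the ANCOVA and the mixed model will often disagree at T1.** Disagreement in 12% (r = 0.5) or 18% (r = 0.7) of trials appears when an adjusted test is set against an unadjusted one. Under the protocol's own zero correlation the figure is 2%. A mixed model that holds the arms to a common baseline mean would, with complete data, give essentially the ANCOVA result. The article does not specify the form.

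**Conclusion.** The contradiction holds and is of moderate weight. Under the sentence as written, the chance of a false PSQI claim at one or both post-baseline visits is about 9-10%, against 5% for the single planned test. It is about 10-12% only if the mixed model also yields a separate T1 test not adjusted for baseline as the ANCOVA is.

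The figures assume two-sided tests, complete data on 64 per arm, and equal correlation of 0 to 0.7 between visits. If the two visit tests were themselves correlated at 0.7, the rate would be 8.4%. They also assume that the PSQI comparisons lie outside the Bonferroni correction. The sample size and the primary estimate are unaffected; what needs repair is the rule that says which result counts.

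**What to change.** Replace the sentence on conclusions in section 4.1 with: *The conclusion on the primary objective rests only on the ANCOVA of PSQI at the preoperative time point (two-sided 0.05). The 6-week PSQI contrast and the mixed-model preoperative estimate are supportive. No between-arm test is made at baseline.*

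If a formal 6-week claim is wanted, the second sentence can instead say that the 6-week contrast is tested at 0.05 only if the preoperative ANCOVA is significant, with the mixed-model preoperative estimate remaining supportive. Either version holds the chance of a false confirmed PSQI claim to at most 5%.

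The cost is one sentence, settled before unblinded data are seen. The T1 test keeps its full 0.05 and its power, and no participants are added. The downside is that a 6-week PSQI effect cannot be claimed as confirmed if the preoperative test fails; under the supportive-only version it is never a confirmatory claim.

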Some strengths of this study include the randomised design with outcome assessors blinded to group allocation. The study will integrate and expand on a gold‐standard multimodal prehabilitation intervention including exercise, nutrition, psychological intervention and smoking cessation delivered by regulated health professionals with several years of experience delivering prehabilitation. The study will capture robust outcomes including demographic, physical and anthropometric, sleep health, clinical and patient‐reported outcomes. The analysis will be conducted using intention to treat. There are limitations to this study worthy of discussion. Selection bias will favour the surgical subgroups referred to the Prehabilitation Program during study recruitment as well as the physicians and patients who refer and accept referral to prehabilitation, respectively. The study will lack a true control group without intervention. This is warranted given the overwhelming evidence supporting prehabilitation. Given that the intervention is delivered by an interprofessional team of allied health professionals, the generalisability of this study to other lower‐resource settings can be considered a limitation. Finally, this study is being conducted without any formal published feasibility trials. As such, it is difficult to predict participant adherence to or satisfaction with the intervention. However, the sleep measures included within this protocol are being used in an ongoing prospective observational study of the same target population with acceptable rates of recruitment, satisfaction and data completeness.

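### Length of stay and complications are compared between arms without regard to type of surgery; stratifying by surgical service would be a cheap gain in precision for these exploratory outcomes

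*Protocol article*

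**What the plan says.** **Tests.** In the Protocol article, section 4.1 (Analytic Plan), the rule is "For outcomes that are measured at only one time point (e.g., length of hospital stay), we will use" a Wilcoxon test for continuous outcomes and a chi-square test for categorical ones. Section 4 (Study Outcomes) lists length of stay, readmission and surgical complications as the clinical outcomes, taken from the medical record up to 90 days after surgery.

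**Adjustment.** The only rule is conditional. If baseline characteristics turn out unbalanced, "the mixed effects models will be adjusted for these potential confounders", with age and sex as examples. Single-time outcomes are not analysed by those models.

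**Case mix.** Sections 3.2 (Participants) and 3.4 (Sampling and Recruitment) admit adults referred to the programme who have surgery scheduled at the centre, and do not restrict the operation. The Discussion acknowledges a mix: "Selection bias will favour the surgical subgroups referred to the Prehabilitation Program during study recruitment". Section 3.5 describes 1:1 randomisation and names no stratification factor.

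**Status.** Section 4.1 calls the secondary outcomes exploratory and applies a Bonferroni correction to them.

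**The concern.** Length of stay and complication risk can be expected to differ between operations. The documents do not quantify this, but it is a reasonable clinical expectation. An unstratified rank or chi-square test leaves those differences in the noise against which the arms are compared. The scheduled operation is known before randomisation, so using it as a stratum costs no data and keeps the error rate.

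The plan accepts in principle that baseline differences may need adjustment. Yet its rule misses the outcomes most closely tied to the operation. The article names the tests itself, so this is a stated choice and not a detail left to a fuller document.

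At stake is the precision of the trial's in-hospital and 90-day clinical comparisons. The primary PSQI analysis is not affected.

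**Working it through.** **1. The plan's own figure.** Section 3.3 gives "Assuming a PSQI score mean of 11.9 (SD 2.6) points for the usual care arm" and says "64 participants per arm (128 total) will be required to detect a difference in mean PSQI score of 1.3 points", that is d = 1.3/2.6 = 0.5.
- Normal approximation: n = 2(1.96 + 0.8416)²/0.5² = 62.8, so 63 per arm.
- With the t distribution: 63.8, so 64. This reproduces the plan.
- 128 × 1.20 = 153.6, so 154 recruited, or 77 per arm.

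This calculation concerns PSQI only. The article states no power for any clinical outcome.

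**2. Inputs for length of stay.** From the plan: 77 per arm (everyone randomised, a best case) and alpha 0.05, taken as two-sided. Assumed, because the documents give none of these:
- log-normal stay in whole days, minimum 1, total SD of log stay 0.9
- log effect −0.25, so exp(−0.25) = 0.78, a stay 22% shorter
- five surgical services with shares 30/25/20/15/10%
- R², the share of variance of log stay explained by surgery type, from 0% to 60%

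**3. Formula check.** SE = 0.9 × √(1 − R²) × √(2/77), and power ≈ Φ(0.25/SE − 1.96). The unstratified test keeps the full SD, which is the R² = 0 row.

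| R² | SE | 0.25/SE | Power | Equivalent n per arm, 77/(1 − R²) |
|---|---|---|---|---|
| 0 | 0.145 | 1.72 | 41% | 77 |
| 0.1 | 0.138 | 1.82 | 44% | 86 |
| 0.2 | 0.130 | 1.93 | 49% | 96 |
| 0.4 | 0.112 | 2.23 | 61% | 128 |
| 0.6 | 0.092 | 2.73 | 78% | 193 |

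This is an upper guide. Rank tests on stays rounded to days, with small strata, do slightly worse.

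**4. Simulation of the tests themselves.** Two-sample rank-sum against van Elteren (weights 1/(N_k + 1), tie-corrected), alpha 0.05:

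| R² | Unstratified | Stratified |
|---|---|---|
| 0 | 38–39% | 36–39% |
| 0.1 | 39–40% | 41% |
| 0.2 | about 37–38% | about 45% |
| 0.4 | about 36–38% | about 54% |
| 0.6 | about 37% | about 73% |

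Type I error was about 5% for both tests. Repeat runs agreed to within about 2 to 3 points.

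**5. Bonferroni.** The number of tests is not given in the article. If it were 10 (alpha 0.05/10 = 0.005), power is about 12% unstratified, against 16%, 23% and 38% stratified at R² of 20%, 40% and 60%.

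**6. Binary outcomes.** Chi-square against Cochran-Mantel-Haenszel, 77 per arm, four equal-sized surgery types, alpha 0.05. All rates and odds ratios are assumed.

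| Outcome (range of rates across types) | Within-type OR | Chi-square | CMH | Gain (points) |
|---|---|---|---|---|
| Complications (10–60%) | 0.5 | 37.0% | 40.7% | 3.7 |
| Complications (5–75%) | 0.5 | 30.2% | 38.4% | 8.2 |
| Complications (10–60%) | 0.35 | 65.7% | 71.2% | 5.5 |
| Complications (5–75%) | 0.35 | 57.3% | 69.6% | 12.3 |
| Readmission (5–20%) | 0.5 | 22.1% | 21.5% | −0.6 |
| Readmission (2–30%) | 0.5 | 21.4% | 21.8% | 0.4 |
| Readmission (5–20%) | 0.35 | 39.2% | 37.8% | −1.4 |
| Readmission (2–30%) | 0.35 | 39.1% | 39.9% | 0.8 |

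For complications the gain is roughly 4 to 12 points, or 13 if powers are first rounded (57% to 70%). For readmission it is about nil. Only an extreme spread of 1–40% gives 2 to 4 points (22.8% to 25.1% at OR 0.5; 41.6% to 45.4% at OR 0.35).

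**The case against.** **No error is shown.** Randomisation makes the unadjusted two-sample tests valid. This stands. A reader might infer that a chance imbalance in surgical mix would bias the result; the documents do not support that, because the test's error rate already allows for chance imbalance. The loss is precision.

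**The outcomes are exploratory.** This also stands. The trial is powered on PSQI alone, and after Bonferroni these comparisons remain underpowered in every scenario computed in step 5. Stratifying helps relative to not stratifying, but does not make them conclusive.

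**The gain may not extend to all three outcomes.** Correct. A reader might infer that readmission loses power in the same way. Under the assumed rates it gains almost nothing, and stratifying can cost slightly when events are sparse.

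**The size is assumed.** Correct. The documents give no case mix, no SD of stay and no prognostic strength. If surgery type explains 10% of the variance or less, the gain is 2 points at most and may be a small loss.

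**Other recovery data exist.** A reader might take the clinical outcomes to be the trial's only evidence on surgical recovery. They are not: PROMIS-29+2 and PSQI are also collected 6 weeks after surgery, and the adjustment rule does reach the mixed models for those.

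**The sentence has a more basic fault.** It names a signed-rank test, which is for paired data and cannot compare two independent arms. That needs correcting whatever is decided here; this point assumes it is done.

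What survives is that the plan fixes a valid but less efficient method, where a better one uses a variable already known before randomisation.

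**Conclusion.** The point holds as a cheap improvement to exploratory analyses, not as an error that threatens the trial. The text is clear: the tests are unadjusted, the operation is unrestricted, and the adjustment rule stops at the mixed models.

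For length of stay the gain at alpha 0.05 is small if surgery type explains 10% of the variance. It grows to about 7 points at 20%, about 16 at 40% and about 35 at 60%, on the assumed SD, effect and strata. With an assumed 10 Bonferroni tests the gains shrink to about 4, 11 and 26 points (16, 23 and 38 minus 12). For complications the gain is modest, and for readmission it is negligible. The documents support no claim of bias, of an inflated error rate, or of harm to the primary PSQI analysis.

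**What to change.** - **Length of stay:** pre-specify the van Elteren test (two-sample Wilcoxon rank-sum, stratified), with strata given by the surgical service of the procedure booked at randomisation.
- **Complications:** pre-specify the Cochran-Mantel-Haenszel test with the same strata.
- **Readmission:** leave unadjusted, or use very few strata, if events are sparse.
- **Strata:** define them from the booked procedure, and pool small services before any outcomes are seen. Apply the stratification whether or not an imbalance is observed.

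The cost is two method names and a short rule for pooling. No new data are needed, since the scheduled surgery is known at referral. The downside is that small services must be pooled, and up to about 2 points of power for length of stay are lost if surgery type is not prognostic.
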